### **3.3 Study procedures**

Overall project duration is 2.5 years, while recruitment period of participants is scheduled for 1 year. Project start is planned for July 2020 after approval by the ethics committee, end of the study is planned for 31 December 2022. Depending on the situation it is planned to involve further sites in Switzerland. Project duration for each patient takes 1 hour for the MRI, 30 minutes for the lumbar puncture and 10 minutes for blood withdrawal. For the hospitalized patients each of the described procedures takes place during hospitalization period. Thus, the participants do not have extra visits at the hospital. Concerning the out-patients we are going to set an appointment for the procedures. The appointment should take place as soon as possible after they received their positive test results, thus during their isolation period. The described procedures are going to take place in a prepared isolation room at the University Hospital of Basel at Klinikum 1 where usually consultation hours take place. The isolation room will be labeled as such and protection clothing will be put in a locker in front of the room. The MRI procedure will be taking place in the same manner as for the hospitalized patients. For precautionary purpose, there will only be one patient at a time and after each appointment the rooms will be cleaned and disinfected according to the usual room cleaning procedures after a hospital stay of COVID-19 infected patients. The appointment will take place during a flexible time band to minimize contact with other people at the hospital and outside.

Material from blood withdrawal and lumbar puncture is going to be frozen at -80° C and stored at the Department of Biomedicine, 4th floor, lab 414, University Hospital Basel, until analysis. Clinical data (neurological examination, neurological scores, laboratory parameters, MRI imaging data) are saved in the clinical information system (ISMED, University Hospital of Basel program for patient's data, and the ICU's proprietary data documentation system) and for further analysis exported in an encoded form to a specific location on the telemedicine software ipath ([www.ipath-network.com/usbnch](http://www.ipath-network.com/usbnch)), which is already in use for the brain tumor data base of the neurosurgical clinic, University Hospital Basel (please refer to REQ-2019-00553). Only designated persons specifically employed for this project will have access to the clinical data saved on this platform.

The autopsy of specific brain regions takes place at the institute of pathology at University Hospital Basel. The tissue of the specific brain regions will be fixed, paraffin embedded and stored at the Department of Biomedicine 4th floor, lab 414, University Hospital Basel, until analysis. For analysis the tissue is subjected to the CODEX workflow by staining with a 50+ Marker panel. This is followed by a complex analysis pipeline which generates single-cell information of specific cell types derived from the multicycle image acquisition.

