### **3.2 Recruitment, screening and informed consent procedure**

Recruitment takes places at University Hospital of Basel. Critically ill patients are going to be recruited at the Intensive Care Unit (ICU), modestly ill patients are going to be recruited from "normal" hospital ward through the project leader.

In case of hospitalized patients that can not be informed, we are going to inform their relatives about the study procedures.

Recruitment procedure is supported from clinical departments of the ICU (Prof. [name]) (critically ill patients) and Internal Medicine (Prof. [name]) (modestly ill patients).

Patients who got tested COVID-19 positive in the ambulatory test centre of the University Hospital of Basel will be handed an information sheet about this project including our contact information. Should they be interested in participating, they can send an email including their name, surname, phone number and date of birth to an email account specifically created for this project ([contact]). Afterwards they will get a phone call, where they will be informed in detail about the procedures that take place and their risks and benefits. If desired we are also able to organize a skype or zoom call.

If they agree, they will receive the patient information and agreement via email or by post and an appointment date will be set for the study procedures. The study agreement has to be printed and signed. The out-patients will have to bring it along to the appointment date for the study procedures. In case they are not in charge of a printer or they forget to bring the signed agreement along, we prepare printed versions of the information and agreement sheet. Then it can be read and signed directly at the University Hospital of Basel during the appointment. For this case we include an extra hour before study procedures start. During this time the out-patients can go through the information again and ask further questions.

Because the out-patients incur a hospital stay only for their participation in this project they will get paid with an amount of 200 CHF.

Concerning the commute to the hospital, we will give precise advice as to how to reach the hospital. We will suggest to take the car, walk or take the bike. Also they will be informed to wear a mask at all times as soon as they leave the house. Should public transport be their only option, they will be excluded from the study. These advices apply for the way home as well.

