# **6 FURTHER ASPECTS**

## **6.1 Overall ethical considerations**

---

 A serious event is defined as any adverse event where it cannot be excluded, that the event is attributable to the sampling of biological material or the collection of health-related personal data, and which:

- a. requires inpatient treatment not envisaged in the protocol or extends a current hospital stay;
- b. results in permanent or significant incapacity or disability; or
- c. is life-threatening or results in death.

Very little is known about COVID-19 pathobiology, its effects on human tissue, its tropism in the human body and its interactions with the immune system. Besides, almost no data exist about the tropism of SARS-CoV-2 within the human body. Although the respiratory tract is thought to be the main virus reservoir, it remains unknown which additional cells of the body are being infected and to what consequences this leads. Moreover, the virus' interaction with the immune system is still poorly characterized, although being particularly important.

Therefore, it is of major importance to identify the mechanisms of SARS-CoV-2 which are leading to infection, severe illness and death. Based on these findings we could identify markers predictive for a severe course. Furthermore, new therapeutic approaches could be generated based on the pathophysiologic mechanisms of this virus, with the result of beneficial treatment response in patients infected with SARA-CoV-2.

In case of incidental findings (MRI images, lumbar puncture, blood withdrawal, neurological state/scores) the participants are informed.

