## **6.2 Risk-Benefit Assessment**

Risks of the procedures in this project:

- MRI: allergic reaction to contrast agents
- Lumbar puncture: Infection, post-lumbar puncture headache
- Blood withdraw: Infection.

Each of the mentioned risks takes place in less than 1%. To reduce the risk of infection the procedures of lumbar puncture and blood withdraw are kept under sterile conditions (disinfection, sterile gloves, protective masks etc.). During MRI procedure the participant is observed by specialized employees.

Results of the project could benefit future patients infected with SARS-CoV-2. We could better understand the mechanisms that take place during infection with SARS-CoV-2, identify predictive markers for severe course and building on these findings new treatment approaches could be generated.

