### 7.2 Data recording and source data

The data of interest in this project is gained from MRI images, CSF, blood plasma and documentation of neurological/mental state/scores. These procedures take only place in case of agreement to this research project. Not all the critically ill COVID-19 patients at ICU have to undergo MRI imaging, evaluation of neurological state and lumbar puncture. According to clinical routine, blood withdrawal is already done.

The documented clinical findings (neurological/mental state/score, MRI images and laboratory parameters) are saved in the University Hospital of Basel software Ismed. Additionally, data relevant for the project (especially basic lab parameters, clinical course, neurological findings including EEG, scores, MRI imaging) is saved in an encoded form in an online repository also used for the brain tumor database of the University Hospital Basel ([ipath-network.com/usbncn](http://ipath-network.com/usbncn)). Only designated coworkers for this project will have access to the data.

The acquired fluids of lumbar puncture, blood withdrawal and autopsy (in case of death) are going to be frozen at -80° C and stored at Department of Biomedicine, 4th floor, Lab 414, University Hospital of Basel.

All ambulatory patients responding to our information sheet will be listed in an excel file which is saved in an encoded form in an online repository also used for the brain tumor database of the University Hospital Basel ([ipath-network.com/usbnch](http://ipath-network.com/usbnch)). Only designated coworkers for this project will have access to the data.

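### Outpatients have one appointment and no planned contact afterwards, so delayed events after lumbar puncture or blood draw reach the project only by unsolicited report

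*Protocol*

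**What the plan says.** **Contact with outpatients.** Protocol section 3.3 states: "Project duration for each patient takes 1 hour for the MRI, 30 minutes for the lumbar puncture and 10 minutes for blood withdrawal". For inpatients it adds that everything happens during the hospital stay. For outpatients it says: "Concerning the out-patients we are going to set an appointment for the procedures". Section 3.2 covers the journey in and then adds: "These advices apply for the way home as well". Outpatients therefore leave after the procedures. Before the appointment, those testing positive at the test centre "will be handed an information sheet about this project including our contact information", and those interested send in a telephone number.

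**Risks.** Section 6.2 lists contrast allergy for MRI, infection for blood withdrawal, and for the puncture: "Lumbar puncture: Infection, post-lumbar puncture headache". All are covered by one figure: "Each of the mentioned risks takes place in less than 1" per cent.

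**Safety rules.** Under section 5.2 the project leader is told within 24 hours when urgent protective measures are needed. Under section 5.3 a serious event interrupts the project, and the Ethics Committee is notified within 7 days. The footnote defining a serious event (printed under section 6.1) covers adverse events whose attribution to sampling or data collection cannot be excluded. Its first criterion is that the event "requires inpatient treatment not envisaged in the protocol or extends a current hospital stay".

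**Data.** Section 7.2 says: "The data of interest in this project is gained from MRI images, CSF, blood plasma and documentation of neurological/mental state/scores". It also lists clinical course among the stored items, without a time window.

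**The concern.** The protocol names risks that can show themselves after the visit and has a strong rule for serious events, but plans no step by which the project would learn of such an event in someone who has gone home. An inpatient remains under observation in the hospital whose records the project uses. An outpatient does not. Of the two limbs of the quoted criterion, an extended current stay hardly applies to an outpatient. What remains is unplanned inpatient treatment, most likely after the appointment and possibly at another hospital. Nobody is assigned to find out about it.

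For outpatients the lumbar puncture is a research exposure: section 3.2 says they come to the hospital only for this project, and section 7.2 says the procedures take place only with agreement to it. If events are not asked about, few or no reported events would not mean that few or none occurred. Early experience could not correct what later participants are told about risk. A headache that is not serious would not start section 5.3, but as listed the data have no place to record it either.

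**Working it through.** **Step 1. The protocol's own figure.** Section 3.3: 60 + 30 + 10 = 100 minutes for the three listed procedures. This is not the whole visit. It leaves out the neurological assessment (sections 2.3 and 3.1) and the optional extra hour for consent (section 3.2). It is a sum of procedure times and does not define an observation period.

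**Step 2. The provisions side by side, for outpatients.**

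| Needed for the safety rule to start | What the protocol provides |
|---|---|
| A time at which delayed events would be seen | One appointment (3.3); no later visit, call or chart check in any section |
| A route by which an event becomes known | Study contact details on the information sheet (3.2); no stated instruction to report |
| A place to record it | Clinical course, with no time window (7.2); no adverse-event item |
| Action once it is known | Stated (5.2, 5.3 and the footnote) |

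The last row is complete. The first three depend on the participant or a third party coming forward.

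**Step 3. How many people.** Section 3.1 plans 20 non-critically ill patients from the ward or the test centre together, without a split. Outpatients therefore number n = 0 to 20 of the 40.

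**Step 4. How many events, at the protocol's ceiling.** Take p = 1% for each risk (section 6.2 says less than 1%, so this is an upper limit) and k = 3 delayed risks: puncture infection, puncture headache and blood-draw infection. Contrast allergy is left out because the point concerns events that appear later.

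- Expected events = n × k × p. For n = 20: 20 × 3 × 0.01 = 0.6. For n = 10: 0.3. For n = 0: none.
- Chance of at least one, risks independent = 1 − (1 − p)^(nk). For n = 20: 1 − 0.99^60 = 45%. For n = 10: 1 − 0.99^30 = 26%.
- If the three risks always fell on the same person, the figure for n = 20 would be 1 − 0.99^20 = 18%, which is also the figure for headache alone (0.2 expected).

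These count events of any severity. The documents give no basis for the share that would meet the serious-event definition.

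**Step 5. Could follow-up here check the figure below 1%?** With zero events in n people, the one-sided 95% upper bound is 1 − 0.05^(1/n): 13.9% for n = 20 and 7.2% for n = 40. Bringing it below 1% would take ln(0.05)/ln(0.99), about 299 event-free participants. Follow-up helps to find events, but it cannot confirm the rate.

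**The case against.** The strongest reply is that the duration sentence in section 3.3 tells participants how much time the procedures take and does not say that involvement ends there. That reading is the natural one. A reader might infer that every participant leaves observation after 100 minutes, but the documents contradict this: death leads to autopsy (sections 2.3, 3.1 and 3.2), clinical course is stored (section 7.2), and participants who regain capacity are asked for their agreement (section 6.3). The point therefore cannot rest on that sentence alone and does not extend to inpatients. It rests on the single outpatient appointment and the absence of any later planned contact.

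A second reply is that passive reporting exists. Outpatients hold the contact details, the serious-event definition has no time limit, and the rules apply whenever an event becomes known. This also stands. A reader might infer that delayed events cannot be captured and that the serious-event rule cannot work for outpatients. The documents support only that detection is unsolicited.

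Third, CRFs are mentioned in section 7.3 but not shown, and the consent pages are not available, so instructions to report symptoms may exist there. That limits the point to what the protocol itself states. It does not supply a scheduled contact.

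Fourth, the figure below 1% is a prior risk statement and not a rate that this project sets out to estimate. It does not fail for want of follow-up, and step 5 shows that 20 to 40 people could not verify it. That one figure covers all the risks without a cited source is a documentation matter and carries no weight here.

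**Conclusion.** The point holds in limited form. For outpatients, 0 to 20 of 40 participants, the protocol names delayed risks and sets a project-interrupting rule, but plans no contact or reporting window that would bring such events to notice. At its own ceiling this concerns up to 0.6 expected events and a 45% chance of at least one. That assumes all 20 non-critical participants are outpatients, a rate of exactly 1% for each of three risks, and independence. Fewer outpatients, lower rates or overlapping risks reduce it.

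A reader might arrive at an 80% chance by counting four risks in all 40 participants (1 − 0.99^160). That includes inpatients, who are not affected by the gap, and contrast allergy, which is not one of the delayed risks considered here. A reader might also picture the outpatients as mostly healthy. The documents describe them only as positive-tested and not critically ill.

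Nothing here affects the exploratory analyses. This is an inexpensive improvement to safety observation and should be made.

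**What to change.** - **Section 3.3:** add a scheduled safety contact by telephone after the procedures for every outpatient. The sponsor should set the timing to suit the risks named in section 6.2.
- **CRF and section 7.2:** add an item recording headache, infection, and unplanned medical contact or admission, including admission to another hospital.
- **Sections 5.2 and 5.3:** state who reviews these records and how they reach the project leader, so that the notification periods can start.
- **Consistency:** reconcile sections 3.3, 5.3, 6.2, 7.2 and the serious-event footnote, and make clear that the duration sentence in 3.3 means procedure time.

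The cost is one or two short calls per outpatient, one CRF item and an amendment. Interested outpatients already give a telephone number (section 3.2) and responders are already listed (section 7.2). The amendment may count as a substantial change that needs ethics approval before use (section 5.5), and the information sheet may need matching text.

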### **Exact description of the body parts**

For this project, specific brain regions of COVID-19 infected and deceased persons, included in this study, are investigated on autopsy specimens from medulla oblongata, cortex, cerebellum, and olfactory bulb. We will include only tissue samples, which have been submitted to the Institute of Pathology, University Hospital Basel.

### **Ban on commercialisation (Art. 9 HFG)**

The bodies or parts of bodies shall not be sold or taken into consideration for any other monetary benefit.

### **3.4 Withdrawal and discontinuation**

Patients can withdraw their consent at any time without giving reasons. There will be no negative consequences. After withdrawal, the collected data and samples remain encrypted. We will use data and the samples until this time point for analysis otherwise the project will lose his value.

## **4 STATISTICS AND METHODOLOGY**

### **4.1. Statistical analysis plan**

This study encompasses a multidimensional exploratory data set of both clinical and biological data. In this Project we are going to collect data sets of 40 participants.

*MRI data:* Imaging data will be analysed by board certified neuroradiologists, and specific encephalitic changes that might be COVID-19 related, will be reported and conjoined with potential neurological symptoms depending on the location of the potential encephalitic lesions. Most importantly, patients that are neurologically affected will be compared to non-affected individuals in terms of CNS involvement.

*Proteomic analysis:* The proteomic biomarkers from an array of cytokines and other inflammatory mediators (CSF and plasma, provided by the company Olink.com) will be compared to control reference sample using descriptive statistics and multivariate comparisons such as clustering algorithms, heatmaps, and correlative analysis. Furthermore, potential treatment effects from antiviral drugs or immune modulators might be taken into considerations.

*Cytof analysis:* Mass cytometry will be performed form peripheral blood mononuclear cells and analyzed with specific platoforms such as immune-Atlas and FlowJo software. High dimensional nearest neighbourhood analysis will be performed (tSNE plots). Cell population frequency and marker expression profile will be potentially correlated to the presence/absence of neurological symptoms and the respective cytokine profile.

*CODEX analysis:* Brain region from deceased patients will be fixed, paraffin embedded and subjected to the CODEX workflow by staining with a 50+ Marker panel. This is followed by a complex analysis pipeline which generates single-cell information of specific cell types derived from the multicycle image acquisition. Images will be segmented, cleaned-up, and cells will be clustered in supervised and unsupervised manner. Global and single marker expression per cell type will be assessed. Cellular neighbourhoods combined with viral distribution will be analyzed. This pipeline is currently implemented at the Department of Biomedicine and pathology and subject to ongoing modifications.

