## 2.2 Primary and secondary endpoints

- Evaluation of neurological/mental state and specific scores
- Systematic CNS MRI imaging to document specific changes due to COVID-19 infection
- Plasma and CSF cytokine targeted proteomics analysis
- Peripheral blood leukocyte CyTOF analysis
- CODEX (high dimensional microscopy) analysis and viral load/in situ distribution analysis of defined regions on brain autopsy specimens

Primary endpoints of this project are the multidimensional integration of the analysis from the procedures described above and assessment of the correlation between the gained clinical data (MRI, mental/neurological state), the body fluid proteomic and mass-cytometric analysis (CSF and Plasma proteomics, peripheral blood mass cytometry) and the CODEX analysis of defined brain regions on autopsy specimens. This will enable us to identify biomarkers that potentially predict CNS involvement of COVID-19 disease and tailor respective treatments.

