## 2.3 Project design

The project flowchart is depicted below. Patients with confirmed COVID-19 disease specifically hospitalized for this disease as well as out-patients will be included. After patient informed consent, we will perform a detailed clinical-neurological assessment followed by blood and lumbar puncture, and MRI analysis. In case of disease-related death (assuming a case fatality rate on the ICU of 50%), an autopsy by the institute of pathology will be performed, encompassing high dimensional analysis of the organs under investigation.

[figure not shown]

**CSF and plasma cytokine proteomics and correlate to mental/neurological state.** CSF will be acquired by lumbar puncture and sent for routine analysis including CSF chemistry, cytology and microbiology. Targeted CSF proteomics using OLINK Proximity Extension Assay (PEA) technology (<https://www.olink.com/products/immune-response-panel/>), to assess a potential

CNS-contribution of the disease will be performed. A similar biomarker approach will be applied for plasma samples from the same time-point as the lumbar puncture. Already established CyTOF technology will be used to gain insight into the peripheral blood immune composition in both patient cohorts (CyTOF panel listed in table 3). Presence of viral RNA will be tested by our in-house qPCR in both plasma and CSF. We will include COVID-19 negative CSF and plasma samples from healthy reference patients into this analysis.

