### **Systematic CNS MRI imaging to document early/manifest encephalitic changes in COVID-19 patients.**

Both patient populations will undergo 3 Tesla magnetic resonance imaging (MRI) in collaboration with our colleagues from neuroradiology (responsible: [name]). MRI sequences will include 3D T1 +/- gadolinium, FLAIR, diffusion, SWI and T2 weighted sequences to document potential early signs of encephalopathy, and will be correlated to CSF, plasma and clinical findings. Appropriate precautions will be taken to ensure the safety in the MRI scanner of patients with respiratory, neurological, or other types of dysfunction, and all necessary anti-infectious precautions will be observed before, during, and after the scanning of patients with known COVID infection.

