## **3 PROJECT POPULATION AND STUDY PROCEDURES**

### **3.1 Project population, inclusion and exclusion criteria**

We will *prospectively* include 20 non-critically ill COVID-19 patients from the inpatient ward or from the ambulatory test centre, and 20 critically ill COVID-19 patients needing mechanical ventilation at the ICU. Neurological assessment will be performed by a board-certified neurologist using NIHSS (National Institute of Health Stroke Scale) scoring and other standard neurological tests. Neurological symptoms will be carefully documented. Assuming a case fatality rate of 50% in the critically ill group, we anticipate to include 10 patients for *post mortem* analysis of brain regions, some of which might be neurologically affected.

The following inclusion criteria are going to be applied: COVID-19 positive tested.

The following exclusion criteria are going to be applied: COVID-19 negative tested, patients under 18 years old, pregnant women.

A pregnancy test is performed and documented for women of childbearing age

Concerning the out-patients they will only be included if they have the option to come to the hospital by car, bike or if they live close enough to walk. In case public transport is their only option they can not be included.

To avoid conflicts and to identify parallel participation of individual USB patients in several studies, the DKF (Departement Klinische Forschung) has created a web application.

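### The protocol neither masks the MRI readers to neurological status nor separates the reading from the symptom linkage, so the MRI comparison of affected with non-affected patients may be inflated

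*Protocol*

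**What the plan says.** Protocol section 4.1 (MRI data) is the only place that describes how scans become data. It states: "Imaging data will be analysed by board certified neuroradiologists". It continues that "specific encephalitic changes that might be COVID-19 related, will be reported and conjoined with potential neurological symptoms depending on the location" of the lesions. The next sentence, introduced as the most important, is that "patients that are neurologically affected will be compared to non-affected individuals in terms of CNS involvement".

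In section 2.3, the paragraph on systematic CNS MRI says the sequences serve "to document potential early signs of encephalopathy, and will be correlated to CSF, plasma and clinical findings".

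The order of assessments is also in section 2.3: after consent, "we will perform a detailed clinical-neurological assessment followed by blood and lumbar puncture, and MRI analysis". Under section 3.1 the neurological state is scored by a different specialist: "Neurological assessment will be performed by a board-certified neurologist using NIHSS (National Institute of Health Stroke Scale) scoring and other standard neurological tests". Section 7.2 places neurological scores and MRI images in the same hospital information system.

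The protocol does not mention masking of MRI readers, a fixed lesion list, the order of reading and linkage, or a definition of CNS involvement.

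**The concern.** Whether a change might be COVID-19 related is a judgement call, and the protocol gives no criteria for it. Symptoms enter the handling of the MRI findings through the location link, and neurological status then defines the two groups compared on CNS involvement. A neuroradiologist who knows of a deficit may search the corresponding region harder, or count a non-specific change that would be passed over in a patient without symptoms. That is review bias. It would push the MRI-neurology association upward without any true relation.

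Two analyses are directly exposed: the affected/non-affected comparison in section 4.1 and the correlation of MRI with clinical findings in section 2.3. If only a clinically informed reading is recorded, the bias cannot be removed afterwards. There is also no internal check on the background call rate, because the COVID-19 negative reference material in section 2.3 is CSF and plasma only.

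**Working it through.** The protocol states no lesion rate, effect size, test or alpha for MRI, so it has no figure to reproduce. The check has two parts.

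**1. Does the plan as written allow an informed reading?**

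- Section 2.3 puts the neurological assessment before the MRI, so the findings exist when the scan is read.
- Section 7.2 keeps both in one system and describes no restriction for readers.
- Section 4.1 asks for a judgement without criteria, followed or accompanied by a link to symptoms.
- No section requires the reading to be finished before the link is made.

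A neuroradiologist who opens the record, reads the scan in the usual clinical way and notes the matching symptom would comply fully. The plan permits the bias. It does not say that readers will work this way.

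**2. How large could the effect be?** All call rates below are assumptions, because the documents give none.

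With no true association, let readers call a change COVID-19 related with probability p in non-affected and p_a in affected patients. The spurious odds ratio is

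OR = [p_a / (1 − p_a)] / [p / (1 − p)].

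- p = 0.10, p_a = 0.20: (0.20/0.80) / (0.10/0.90) = 2.25
- p = 0.10, p_a = 0.30: (0.30/0.70) / (0.10/0.90) = 3.86

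In patients, if the 40 were split 20/20, these are 2 against 4 and 2 against 6 positive calls (20 × 0.10, 20 × 0.20, 20 × 0.30).

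A wider set of assumptions shows how often a test would mislead. It uses the protocol's 40 participants (20 + 20), with 10, 20 or 30 of them neurologically affected, p = 0.20, 0.30 or 0.40, and p_a = p + s. The rejection rate is the exact binomial probability of all tables with a two-sided Fisher p-value of 0.05 or less. The test and level are also assumptions.

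| Shift s in call rate | Spurious OR | Rejection rate |
|---|---|---|
| 0 | 1.0 | 2.3% to 2.8% |
| 10 points | 1.5 to 1.7 | 4.6% to 7.1% |
| 20 points | 2.3 to 2.7 | 12% to 19% |
| 30 points | 3.5 to 4.0 | 27% to 41% |

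A 10-point shift roughly doubles or triples the test's own no-shift rate but leaves it near 5%. Shifts of 20 to 30 points produce a misleading result in about one to four trials in ten.

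**The case against.** A reader might infer that reading and linkage are one unblinded step, and that the association is therefore built in by the reading. The documents do not support this. The wording in section 4.1 can equally mean that the report is written first and the link made afterwards. The link as described runs from lesion location to symptom and not the other way. Nothing says symptoms decide whether a change counts as a lesion. A neurologist, not the MRI reader, scores the neurological state (section 3.1), and nothing shows that MRI is used to form the affected group. Dependence arises only if readers see and use the clinical findings.

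A reader might also infer that the primary endpoint as a whole is inflated. Section 2.2 describes "assessment of the correlation between the gained clinical data (MRI, mental/neurological state" as one group and then lists the body-fluid and autopsy data as the other elements. MRI and neurological state thus stand together, and knowing the symptoms does not directly inflate a correlation with proteomics or autopsy findings.

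Three further objections have some weight:

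- **Reading rules may sit in an SAP or imaging manual that is not shown.** This is fair for detail such as a lesion checklist. But section 4.1 itself sets out the reading and linkage, and as written an informed reading complies with it.
- **The study calls itself exploratory.** That bears on how a p-value is used. It does not protect against a measurement that depends on the group being compared.
- **The sizes rest on assumed call rates.** This stands in full. They show scale only, and at a 10-point shift the rejection rate stays close to 5%.

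**Conclusion.** The concern holds as a risk, not as a demonstrated bias. Section 4.1 relies on a call without criteria, links it to symptoms and uses it in the comparison the protocol ranks highest, on an undefined outcome. It neither masks the readers nor fixes the reading before the linkage. The affected/non-affected MRI comparison and the MRI-clinical correlation in section 2.3 may therefore be inflated.

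The size is unknown. The odds ratios of 2.3 to 3.9 assume no true association, a 10% call rate in non-affected patients, and 20% to 30% in affected patients because readers know the symptoms. None of these rates comes from the documents. Confidence is medium, because reading rules may exist elsewhere. The change is still worth making, since it is cheap and the bias cannot be undone once only an informed reading exists.

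**What to change.** Amend section 4.1 (MRI data) as follows:

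1. The existing neuroradiologist first completes a fixed checklist for each scan (lesion type, region, enhancement, encephalitic change yes/no) without neurological findings, cohort or laboratory results.
2. The checklist is locked before that reader sees any clinical information or writes the unblinded clinical report. Locking it only before the data are merged is not enough, because a reader who has already seen the record is no longer masked.
3. MRI CNS involvement is defined from the locked checklist alone, without reference to symptoms, and this reading is used in all comparisons and correlations.
4. The linkage of lesion location to symptoms is a separate, later step and is reported as such.

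Clinical reporting and the handling of incidental findings (section 6.1) stay unblinded and must not be delayed. If a scan has to be reported clinically first, another of the neuroradiologists who has not seen the record could complete the checklist, with the reading order recorded.

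The cost is a one-page form and a lock step for existing readers. No sample size changes. Masking to ICU status may be imperfect, because it can sometimes be visible on the scan.
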